### Outcomes {12}

The research inquiry will encompass an assessment of both primary and secondary outcomes. The primary outcome directed towards the evaluation of POSAS 3.0 scores. Throughout the study’s duration, we will systematically assess POSAS 3.0 scores at four specific time intervals: the initial baseline assessment upon participants’ first arrival, followed by subsequent evaluations at weeks 4, 8, and 12. This measurement directly correlates with the patient’s quality of life [52]. We will utilise the most up-to-date version of the POSAS 3.0 questionnaire, accessed at https://www.posas.nl. We have received approval from the POSAS team to use this questionnaire and have been granted a license via email. This questionnaire will be translated into Indonesian and tested for validity and reliability before being used in the study. Patients will complete the POSAS 3.0 questionnaire, which includes 16 items. Five of these items are about the current state of their scar tissue, and 11 questions are about how their feeling related to the scar tissue over the past week. Meanwhile, an observer will complete a different section of the questionnaire with seven items scored on a scale of 1 to 5. We will add the PSAS and OSAS scores to determine the total score. The minimum patient score is 16, while the highest score is 80. The minimum and maximum scores for observers are 7 and 35, respectively.

In the context of this study, secondary outcomes encompass the evaluation of erythema and pigmentation levels, as well as assessments of keloid area, thickness, and pliability. These secondary outcome measures at four different time points will be assessed concurrently with the primary outcome.

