### Sample size {14}

The sample size determination depends on the specific criteria for comparative research. The variable type of the primary outcome data plays a significant role in deciding the appropriate sample size [50, 51, 53, 54]. The primary outcome is the changes in POSAS 3.0 scores, considered continuous data. Effect size measurement will be the mean difference. The research involved unpaired or two groups receiving different treatments, with the outcome being measured multiple times. As a result, a specific formula was utilised below [55].

This study maintains a 5% type I error dan is powered to have an 80% chance of detecting a minimum of 4 different scores of POSAS. Thus, a sample size of 18 was calculated for the two-sided approach. Adjusted sample size to anticipate a 20% dropout is obtained from the formula N1 = *n*/(1-d), with *n* as the sample size required per formula and d as the dropout rate [56]. Thus, the final sample will be 23 for each group treatment.$${n}_1={n}_2=Y\left[2{\left(\frac{\left[{z}_{\alpha }+{z}_{\beta}\right]s}{x_1-{x}_2}\right)}^2\right]$$

*Z*
_*α*_ = 5% (1.96), *Z*_*β*_ = 20% (0.84), *S* (standard deviation) = 4.8, *x*1-*x*2 (the minimum difference in POSAS scores between the two treatment groups) = 4, *Y* (correction factor for multiple assessments) = 0.8.

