## Statistical methods

### Statistical methods for primary and secondary outcomes {20a}

Statistical analysis will be done by Statistical Package for Social Science (SPSS) version 24. An analysis of the demographic data of the research subjects is planned to be conducted using descriptive statistics. The findings presentation will utilise frequency and percentage tables. Mean values are presented with standard deviation for continuous variables with a normal distribution. The normality of the data can be determined using the Shapiro-Wilk test. If the distribution is not normal, the median and interquartile range (IQR) are used. We conduct an analysis that compares the efficacy of a numerical variable in two groups and within a group, measured multiple times, using a generalised linear model analysis with alternative repeated Mann-Whitney analysis. Our study focuses on continuous variables for both primary and secondary outcomes. Our test had a power value of 80%, a confidence interval of 95% (95% CI), and a significance level of *p* < 0.05.

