### Methods in analysis to handle protocol non-adherence and any statistical methods to handle missing data {20c}

Our analysis will involve intention-to-treat analysis (ITT) to address non-adherence among participants, along with multiple imputations to handle any missing data. Additionally, we will thoroughly report the reasons for withdrawal within each randomisation group and qualitatively compare them. To ensure accuracy, we will combine all completed and imputed datasets and utilise Rubin’s multiple imputation method with five datasets to estimate the treatment effect.

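### The primary analysis offers two methods with no rule for choosing, no deciding contrast and no control across visits, so the stated 5% error and 80% power are not secured

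*Protocol article*

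**What the plan says.** The Protocol article, Outcomes {12}, makes POSAS 3.0 the primary outcome and will "systematically assess POSAS 3.0 scores at four specific time intervals": baseline and weeks 4, 8 and 12. Sample size {14} and Plans for assessment {18a} describe the outcome as change in POSAS, but neither names the visit or effect that decides the trial.

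Statistical methods {20a} describes an analysis that "compares the efficacy of a numerical variable in two groups and within a group", measured repeatedly, "using a generalised linear model analysis with alternative repeated Mann-Whitney analysis". The significance level is p < 0.05, with no adjustment across visits.

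Sample size {14} says: "This study maintains a 5% type I error". It adds that the trial is "powered to have an 80% chance of detecting a minimum of 4 different scores of POSAS" and that "a sample size of 18 was calculated for the two-sided approach". The calculation includes a factor Y = 0.8 for multiple assessments.

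Section {20c} plans Rubin's "multiple imputation method with five datasets to estimate the treatment effect".

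**The concern.** The protocol does more than leave detail to a later plan. It writes in two competing primary methods, and one of them is a test repeated over visits. Three things follow.

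- **Error rate.** With no deciding contrast, nothing in the text stops a significant result at week 4, 8 or 12 from being presented as the trial's answer. The 5% level would not hold under that reading.
- **Power basis.** The sample size takes a 20% saving for repeated measurement. One analysis that combines visits can earn that saving; separate tests at each visit cannot.
- **Missing data.** Section {20c} promises a pooled treatment effect. A Mann-Whitney U or p-value is not an estimate with a standard error, and the protocol does not say what would be pooled if the alternative were used.

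The fallback also makes no covariate adjustment for baseline POSAS, although baseline is collected for everyone.

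**Working it through.** **Inputs from Sample size {14}:** two-sided 5% (z = 1.96), 80% power (z = 0.84), SD 4.8, difference 4, Y = 0.8, dropout 20%. From Outcomes {12}: four assessments, three of them after baseline. The between-visit correlation ρ is not stated, so it is an assumption and a range is shown.

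**1. The plan's own figure.** Without Y: 2 × ((1.96 + 0.84) × 4.8 / 4)² = 2 × 3.36² = 22.58. With Y: 0.8 × 22.58 = 18.06, stated as 18. With dropout: 18 / 0.8 = 22.5, so 23. The figure is reproduced (strict rounding up would give 19, a trivial difference).

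**2. A plausible ρ.** If Y is the usual variance factor for a mean of m equally correlated visits, Y = [1 + (m − 1)ρ] / m. Then ρ = (0.8m − 1)/(m − 1), which is 0.70 for m = 3 and 0.73 for m = 4. The protocol does not give this formula, so 0.7 is an inference.

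**3. Chance of at least one p < 0.05 over three post-baseline visits, with no true difference.** The independent-test bound is 1 − 0.95³ = 14.3%. With equal correlation between visits (normal approximation, simulated):

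| ρ | 0.3 | 0.5 | 0.7 | 0.8 | 0.9 |
|---|---|---|---|---|---|
| any of three visits | 13.6% | 12.5% | 10.9% | 9.8% | 8.3% |

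Simulating the Mann-Whitney tests themselves with 23 per arm gives about 8 to 13% over this span. At ρ = 0.7 the result is 10.9% on raw scores and 12.5% on change from baseline. A single pre-named week-12 test gives about 5%.

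**4. Power at a single visit, without Y, difference 4, SD 4.8.** The standardised signal at 18 per arm is 4 / (4.8 × √(2/18)) = 2.5.
- Combined analysis with Y: 2.5 / √0.8 = 2.80, power 79.8%.
- t test at one visit: about 68% (noncentral t).
- Mann-Whitney on raw scores, efficiency 3/π: 2.5 × √(3/π) = 2.44, power about 69% (normal approximation).
- Mann-Whitney with 23 per arm, if nobody drops out: about 79%.

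**5. Power of a baseline-adjusted week-12 contrast.** Its variance factor is about 1 − ρ². This is at or below 0.8 once ρ ≥ √0.2 = 0.45. At 18 per arm (noncentral t), power is 72% at ρ = 0.3, 80% at 0.5 and 93% at 0.7.

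**The case against.** The strongest reply is that the text can be read more kindly, and much of that reply stands.

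- **Any-visit success.** No section says that a significant result at any visit would count. Trial design {8} and {18a} point towards change over 12 weeks up to the final assessment. They point that way but do not fix it, so the error inflation is conditional.
- **A normality-driven switch.** A reader might infer that Shapiro-Wilk decides between the two methods. Section {20a} ties that test only to reporting mean and SD or median and IQR. What can be said is that no switching rule is given.
- **Baseline ignored.** A reader might infer that the rank test discards baseline. The outcome is described as change, and a rank test on change scores uses baseline by subtraction. Only covariate adjustment is absent, and the protocol does not promise that for the model either.
- **Pooling impossible.** This goes too far. A rank-based estimate with a standard error could be pooled. The protocol simply does not say what would be.
- **Model route.** A reader might infer that the generalised linear model ignores within-patient correlation, or dilutes the effect by averaging over baseline. It is applied to a repeatedly measured variable, so a repeated-measures model is probably meant, and the protocol never specifies a main effect that includes baseline.
- **Within-group comparison.** The trial is a parallel-group superiority design, and no within-arm success criterion is set.

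The core is untouched: two methods, no choice rule, no deciding contrast, no control across visits, and a fallback that does not match the sample size.

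**Conclusion.** The point holds in this limited form. Section {20a} leaves both the primary method and the deciding contrast open, and one permitted branch is repeated testing at 5%. If any post-baseline visit could decide, the type I error would be 8.3% to 13.6% for ρ from 0.9 to 0.3, and about 11% at the correlation suggested by Y. That rests on an any-visit rule that the protocol neither states nor excludes, and on assumed correlations.

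Separately, the visit-by-visit fallback has about 68 to 69% power at 18 per arm for a single visit on raw scores, taking 4.8 as the SD of the score tested. The planned 80% depends on Y, which that fallback does not earn. The mismatch with Rubin's rules is a gap in specification rather than an impossibility. The sample-size arithmetic itself is not at fault.

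**What to change.** In {20a}, state one primary analysis: a linear mixed model for repeated measures on total POSAS at weeks 4, 8 and 12, with baseline POSAS as covariate, treatment, visit, treatment-by-visit and a within-patient covariance. The single deciding test is the losartan gel minus triamcinolone difference at week 12, two-sided 5%, with its 95% CI. In {20c}, name this difference as the estimate pooled over the five imputed datasets.

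Make weeks 4 and 8 supportive. Keep any Mann-Whitney or rank-ANCOVA as a sensitivity analysis only. Report within-arm change descriptively, without calling it efficacy, since there is no untreated arm.

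The cost is rewording, with no new data and little extra analysis; it should be settled before any unblinded analysis. The price is that week 4 or week 8 alone can no longer support a success claim. Power for the week-12 contrast also depends on the baseline correlation, as shown in step 5 of the working.

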### Interim analyses {21b}

Not applicable. An interim analysis is unnecessary due to established product safety, a small number of participants, and a short study period.

### Methods for additional analyses (e.g. subgroup analyses) {20b}

Additionally, we evaluated the level of agreement between patients and observers on scar tissue assessments using POSAS 3.0 by calculating the Pearson correlation coefficient. When analysing the impact of keloid duration on treatment outcomes, Spearman’s correlation coefficient is utilised with a significance level of *p* < 0.05.

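### Patient–observer agreement on POSAS 3.0 is to be judged by Pearson correlation, which measures linear association and cannot show a systematic difference between raters (minor; additional analysis)

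*Protocol article*

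**What the plan says.** Methods for additional analyses {20b} gives both the aim and the method: "we evaluated the level of agreement between patients and observers on scar tissue assessments using POSAS 3.0 by calculating the Pearson correlation coefficient". The article names no agreement statistic and no rescaling. The section does not say whether totals, single items or changes are correlated, or at which visit.

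Outcomes {12} describes the two parts of the instrument:

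- **Patient part.** "Patients will complete the POSAS 3.0 questionnaire, which includes 16 items". Of these, "Five of these items are about the current state of their scar tissue"; the other 11 ask about feelings related to the scar over the past week. "The minimum patient score is 16, while the highest score is 80".
- **Observer part.** "an observer will complete a different section of the questionnaire with seven items scored on a scale of 1 to 5". "The minimum and maximum scores for observers are 7 and 35, respectively".

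The two scores are then added to give the POSAS total. No correspondence between patient items and observer items is stated.

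**The concern.** Agreement asks whether two raters give the same value. Pearson's r asks only whether the pairs lie close to a straight line with non-zero slope, whatever its intercept and slope. Followed as written, the plan could report a high r as good agreement when observers consistently score milder, or more severely, than patients.

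There is a second difficulty. A comparison of totals has no common ground on which agreement could be defined, because the two parts differ in number of items, range and content. Replacing r with an agreement coefficient on the totals would therefore not repair the analysis.

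What is at stake is the wording of one additional result in the trial report.

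**Working it through.** **Inputs.** Numbers of items and score ranges are from Outcomes {12}. The aim and statistic are from {20b}. The illustrations use n = 46, from Sample size {14}, where "the final sample will be 23 for each group treatment" (2 × 23 = 46). The scores in steps 3 and 4 are constructed and are not trial data.

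**1. Reproduce the stated ranges.** Items × 1 to items × 5:

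- Patient: 16 × 1 = 16; 16 × 5 = 80. Matches.
- Observer: 7 × 1 = 7; 7 × 5 = 35. Matches.

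The ranges are consistent with 1–5 scoring of every item in both parts.

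**2. What r ignores.** Let the observer score be y = a + b·x with b > 0. Then cov(x, y) = b·var(x) and sd(y) = b·sd(x), so r = b·var(x) / (sd(x) · b·sd(x)) = 1 for every a and every positive b. Neither a constant nor a proportional difference between raters can lower r.

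**3. Constant shift on a common 1–5 scale.** Take patient values x evenly spaced from 2 to 5 (46 points), and y = x − 1.

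- Pearson r = 1.00.
- Variance of each score (divisor n) = (3²/12) × (47/45) = 0.783. Mean difference, observer minus patient = −1.
- Lin's concordance = 2·cov / (var x + var y + (mean difference)²) = (2 × 0.783) / (2 × 0.783 + 1) = 1.567 / 2.567 = 0.61.
- Absolute-agreement ICC (two-way, single measure) = 0.62.
- Limits of agreement: the difference has SD 0, so both limits equal −1.

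The raters never agree, r is perfect, and the agreement statistics show the gap.

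**4. Why totals have no common scale.** Suppose both raters have the same item mean q. The totals are 16q and 7q, and they differ by 9q.

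| Item means | Pearson r | Difference in totals | Concordance | ICC |
|---|---|---|---|---|
| 1 to 5 | 1.00 | 9 to 45 (mean 27) | 0.27 | 0.27 |
| 2 to 4 | 1.00 | 18 to 36 (mean 27) | 0.09 | 0.10 |

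For item means 1 to 5, var q = (4²/12) × (47/45) = 1.393. Concordance = (2 × 112 × 1.393) / ((256 + 49) × 1.393 + 27²) = 311.9 / 1153.7 = 0.27.

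An agreement coefficient on raw totals would thus look poor even when the item means are identical. This shows that agreement between totals is undefined here. It does not show that r is wrongly computed on them, since r is scale-free.

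**5. Content.** Eleven of the 16 patient items, or 69%, concern feelings, while the observer fills in a separate seven-item section. Dividing the totals by 16 and by 7 would equalise the range but not the content, and a difference between the two means would mix rater differences with differences in what was asked.

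**The case against.** The strongest reply is that this is a peripheral analysis. It sits among the additional analyses, no decision depends on it, and replacing one word would remove the mismatch. The scale is also used because it brings in both patients' and doctors' perspectives (Plans for assessment and collection of outcomes {18a}), so a divergence between the two is not in itself an error. This stands, and it holds the severity to minor. It does not remove the defect, because the article itself pairs agreement with Pearson's r; this is not a detail left to an analysis plan.

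A reader might infer more than the text supports:

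- **That unequal ranges invalidate r.** They do not. Correlation is unaffected by positive rescaling. The ranges matter only if agreement between totals is claimed.
- **That raw totals will certainly be correlated.** {20b} does not say so. Totals are a reasonable inference, since they are the scores for which Outcomes {12} gives ranges, but the main point holds for any choice of scores.
- **That the primary outcome is compromised**, because patients are unblinded (Who will be blinded {17a}) and their score is added to the observer's. The sum does not depend on agreement. No patient–observer statistic, of whatever kind, changes the primary estimate or separates unblinding bias from a genuine difference in perspective.

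The shift of one point in step 3 is likewise a demonstration of a property of r, not an estimate for this trial. It presumes values that can be paired on a common scale, and the article states no such pairing.

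**Conclusion.** Wrong as written, and minor. {20b} states an agreement aim and assigns it a statistic that cannot detect systematic disagreement: a constant shift still gives r = 1. The two parts of the questionnaire, as described, offer no shared item set or total scale on which agreement of totals could be assessed.

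The first conclusion is algebraic and needs no assumption about the data. The coefficients 0.61, 0.62, 0.27 and 0.09–0.10 depend on the constructed scores and would change with their spread. The second conclusion rests on the description in Outcomes {12}. The primary comparison, the summed POSAS score and the sample size are unaffected.

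**What to change.** Change one sentence in Methods for additional analyses {20b}, by either route:

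1. **Keep Pearson.** Describe the result as the correlation between patient and observer scores, and make no claim of agreement. This cures the mismatch fully.
2. **If agreement is wanted,** restrict it to scar features that patient and observer both rate on the same 1–5 scale, and list those features. Report weighted kappa or an absolute-agreement ICC, with the mean difference and limits of agreement. Whether such matching features exist must be checked against the questionnaire, because the article does not list the items.

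Do not put an ICC or limits of agreement on the patient total divided by 16 against the observer total divided by 7, for the reason in step 5. Whichever route is taken, the same sentence should say which scores and which visit are used.

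Cost: a wording change for route 1; for route 2, also a short list of matched items. Neither needs new data or more participants.

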### Methods in analysis to handle protocol non-adherence and any statistical methods to handle missing data {20c}

Our analysis will involve intention-to-treat analysis (ITT) to address non-adherence among participants, along with multiple imputations to handle any missing data. Additionally, we will thoroughly report the reasons for withdrawal within each randomisation group and qualitatively compare them. To ensure accuracy, we will combine all completed and imputed datasets and utilise Rubin’s multiple imputation method with five datasets to estimate the treatment effect.

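### Five imputed datasets are too few for a stable p-value near 0.05 when 20% dropout is planned for, and the Mann-Whitney alternative has no stated estimate and standard error to pool

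*Protocol article*

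**What the plan says.** Section {20c} plans an intention-to-treat analysis "along with multiple imputations to handle any missing data". It then fixes both the number of imputations and the pooling rule: Rubin's "multiple imputation method with five datasets to estimate the treatment effect".

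Section {14} (Sample size) shows how much missing data the trial expects: "Adjusted sample size to anticipate a 20% dropout". It sets the error rate ("This study maintains a 5% type I error"), a two-sided approach and 80% power, and names the mean difference as the effect measure.

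Section {20a} analyses the repeated measurements with a generalised linear model, with an "alternative repeated Mann-Whitney analysis", and sets significance at p < 0.05. It does not say which estimate and standard error would accompany the rank-based alternative.

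**The concern.** Multiple imputation is itself a simulation. With m datasets, the pooled estimate and its between-imputation variance both carry random error that depends on the seed and shrinks as m grows. With m = 5 the between-imputation variance rests on only four degrees of freedom. If about a fifth of the final scores are missing, this noise may be large enough to move a near-threshold p-value across 0.05, so the same trial data could be declared significant on one run and not on the next.

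The second issue is fit between methods. Rubin's rules combine an estimate with its variance. A Mann-Whitney test as named yields a U statistic or a p-value. If the alternative were used, presumably when normality fails, the protocol does not say what would be pooled over the imputed datasets.

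**Working it through.** **The plan's own figure.** From section {14}: n = 0.8 × 2 × [(1.96 + 0.84) × 4.8 / 4]² = 18.06, stated as 18. With dropout, 18 / (1 − 0.20) = 22.5, rounded up to 23 per arm. This reproduces. Twenty per cent of 23 is 4.6, so about 5 patients per arm may lack a week-12 score.

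**Inputs.**
- From the documents: m = 5, 46 patients, two-sided 0.05, 20% planned dropout.
- Assumed: complete-data degrees of freedom ν = 43 (46 patients minus intercept, treatment and baseline) and an FMI of 0.10 to 0.21. The upper value is close to the raw missing share, 5/23 = 0.217. The lower value stands for less dropout, or for imputation that draws much information from the week 4 and 8 scores.

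**Formulas.** Scale the converged (infinite m) total variance to 1, so the within-imputation variance is W = 1 − FMI and the between-imputation variance is B = FMI.
- Simulation error of the pooled estimate, as a share of its standard error: √(FMI/m).
- Relative efficiency: 1/(1 + FMI/m).
- For one run: estimate = t₀ + N(0, B/m), where t₀ is the converged t; b = B·χ²(m−1)/(m−1); T = W + (1 + 1/m)b; λ = (1 + 1/m)b/T.
- Barnard-Rubin degrees of freedom: 1/[λ²/(m−1) + 1/ν_obs], with ν_obs = ν(1 − λ)(ν + 1)/(ν + 3).

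The converged degrees of freedom are 43 × (44/46) × (1 − FMI), that is 37.0 at FMI 0.10 and 32.5 at FMI 0.21. For a converged p of 0.05, t₀ is 2.026 and 2.036 respectively.

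**Results** (400,000 runs per row):

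| FMI | m | Error/SE | Relative efficiency | Converged p = 0.05: central 95% of p | Converged p = 0.03: runs not significant |
|---|---|---|---|---|---|
| 0.10 | 5 | 0.141 | 0.98 | 0.026–0.103 | 13% |
| 0.10 | 50 | 0.045 | 0.998 | 0.041–0.062 | <1% |
| 0.21 | 5 | 0.205 | 0.96 | 0.017–0.155 | 29% |
| 0.21 | 50 | 0.065 | 0.996 | 0.036–0.070 | <1% |

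**Away from the threshold**, at FMI 0.21 and m = 5, 86% of runs are significant when the converged p is 0.02, 96% when it is 0.01 and 99% when it is 0.005.

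**Check with simulated trials** (23 per arm, 5 per arm missing week 12, difference 4, SD 4.8, assumed within-patient correlation 0.5 or 0.7, random dropout). The between-imputation share of the variance was about 0.21 to 0.25. More than 5% of seeds reversed the decision in 17% to 38% of trials with m = 5 and in 0% to 8% with m = 50. These shares are rough: 40 datasets per setting for m = 5 and 25 for m = 50, each with 30 seeds.

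**The alternative test.** Section {20c} promises a pooled treatment effect, and section {14} defines that effect as a mean difference. The generalised linear model supplies one, with a standard error. The Mann-Whitney alternative in section {20a} is given neither.

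**The case against.** Every finite number of imputations depends on the seed, including 50, so seed dependence alone is no defect. That is correct; the point is its size.

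A reader might infer that the trial's conclusion is largely decided by the seed, and cite that at a converged p of exactly 0.05 only 42% of five-imputation runs fall below 0.05 (FMI 0.21). That share is no evidence against five: it is 47% with 50 imputations, because about half the runs fall on each side at any m. Only the width of the range is informative. In some 62% to 83% of the simulated trials at the design effect, the seed hardly mattered with m = 5.

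An FMI of 0.21 is also at the high end. POSAS is scored at weeks 4, 8 and 12, and if dropouts had weeks 4 and 8 observed, the FMI would be about 0.11 to 0.17 (assumed correlations 0.7 to 0.85). The 20% is a planning allowance, and the protocol provides weekly calls, reminders, rescheduling and transport fees. This stands, and it is why the range down to 0.10 is shown; even there, five imputations give 0.026 to 0.103.

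A reader might also infer that Mann-Whitney results cannot be pooled and that no valid treatment effect would exist in the non-normal case. The documents do not support that. The mean difference can be pooled whichever test is used, rank-based estimates with a standard error exist, and the protocol nowhere says that Rubin's rules will be applied to Mann-Whitney p-values. What stands is that the stated alternative has no stated poolable quantity.

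Finally, the imputation variables and the seed may be in an analysis plan that is not shown, so their absence is not held against the protocol. The number five is different: the protocol states it.

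**Conclusion.** The point holds in limited form. Five imputations are too few for a reproducible p-value if about 20% of scores are missing and the result lies near 0.05; 50 remove most of the instability. A converged p of 0.03 would be missed in roughly one run in eight (FMI 0.10) to more than one in four (FMI 0.21) with five imputations, and almost never with 50. The treatment estimate itself loses only about 2% to 4% efficiency, and a clear result would be little affected. The figures rest on the assumed FMI, the assumed 43 complete-data degrees of freedom and approximate normality of the estimate; lower dropout would shrink them. The gap between the Mann-Whitney alternative and Rubin's rules is a lesser matter of specification and does not make the plan unworkable. The change is worth making because it improves a stated method at almost no cost.

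**What to change.** In section {20c}, replace five imputed datasets with at least 50, with the random seed set in advance (here or in the analysis plan). State that Rubin's rules are applied to the model-based mean difference and its standard error, the effect measure already named in section {14}. If the rank-based alternative is kept, name a rank-based estimate that has a standard error, such as the probability index (the chance that a patient in one arm scores better than a patient in the other), and pool that instead of the Mann-Whitney p-values. The cost is a sentence or two of text and seconds of computing; the sample size and data collection are unchanged.
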